### Clinic Tasks

• Visual probe task

• At the baseline session and again at 4 weeks post-quit, 8 weeks, 3 months and 6 months, all participants complete the assessment version of the visual probe task. The assessment version, which will be used to measure attentional bias, comprises a total of 192 trials, presented in two blocks. Each trial begins with a fixation cross displayed in the centre of the computer screen for 500 ms. A picture pair of smoking-related and neutral pictures is then presented side-by-side on the screen for 500 ms. After this picture pair disappears, a visual probe is presented in the location formerly occupied by one of the pictures. This probe is either a circle or square. Participants are required to discriminate the identity of the probe and respond accordingly by pressing the up or down arrow keys on the keyboard as quickly as possible. There is a 500 ms interval before the next trial. Presentation of each picture-pair and probe location is counterbalanced. In all trials, the visual probe replaces the smoking-related and neutral pictures with equal frequency. At the start of the task, participants carry out 8 practice trials in which neutral picture pairs are presented first, to allow them to become familiar with the procedure.

• Each block of trials is presented in a new random order for each participant, using EPrime version 2 (Psychology Software Tools Inc., Pittsburgh PA). The task takes approximately 16 minutes. Attentional bias scores will be calculated from reaction time (RT) data; an attentional bias towards smoking cues is characterized by faster reaction times towards smoking-related pictures than neutral pictures.

• Pictorial Stroop task

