• All participants will carry out a pictorial Stroop task as an additional measure of cognitive bias. The pictorial Stroop task will be given after the visual probe task at the baseline session and again at 4 weeks post-quit, 8 weeks, 3 months and 6 months. The task comprises a total of 192 trials, presented in four blocks of 48 trials, with each block consisting of smoking-related pictures or neutral pictures only. Each picture is presented centrally on a computer screen with either an outline of a red, blue, yellow or green border. Participants are required to indicate the colour of the border, while ignoring the picture, by pressing one of four corresponding labelled keys on the keyboard, as quickly as possible. Participants receive 8 practice trials in which neutral pictures are presented first, to allow them to become familiar with the procedure. A short break between blocks will be permitted.

• Each block of trials is presented in a new random order for each participant, using EPrime version 2 (Psychology Software Tools Inc., Pittsburgh PA). The task takes approximately 12 minutes to complete. Stroop bias scores will be calculated from RT data; selective processing of smoking cues is characterized by slower reaction times towards smoking-related pictures than neutral pictures.

• Cue exposure task

• At 1 week prior to quit day, 4 weeks post-quit and follow-up sessions at 8 weeks, 3 months and 6 months, participants in both groups will be given a cue exposure procedure to measure cue-induced craving immediately after completion of the visual probe task and pictorial Stroop task. This is a common procedure in cue-reactivity research [49,50]. Showing a strong craving response to cue-exposure has been shown to predict relapse risk [51]. Prior to attending the session at week −1, participants will be instructed to abstain from smoking for at least 1 hour. We chose an abstinence period of 1 hour to avoid floor effects in craving ratings, commonly found immediately after smoking [52].

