### Other trial outcomes

• Feasibility of running the ARTS trial within NHS SSS assessed on the basis of:

• - Rates of response to patient invitation letters;

• - Rates of recruitment at telephone screening;

• - Rates of attendance at clinic visits;

• - Rates of drop out prior to and after randomisation.

• User acceptability as measured by ratings of perceived usefulness on a patient satisfaction questionnaire.

• Change in cue-induced cravings measured on the VAS prior to and at the end of the cue-exposure task at 4 weeks, 8 weeks, 3 months and 6 months post-quit day in abstinent and non-abstinent smokers across both trial arms.

• Measure of cognitive processing bias on the pictorial Stroop task, to assess generalisation of AR effects at 4 weeks post-quit in abstinent and non-abstinent smokers across both trial arms. Stroop bias will be measured by the difference in median reaction time taken to respond to colour-naming of smoking-related stimuli versus colour-naming of neutral stimuli.

• Measure of attentional bias towards novel untrained stimuli on the visual probe task at 4 weeks post-quit in abstinent and non-abstinent smokers across both trial arms.

• Measure of attentional bias on the visual probe task and pictorial Stroop task at 8 weeks, 3 months and 6 months to assess long term effects of AR.

• Strength of urge to smoke and withdrawal symptoms on the MPSS, measured up to 8 weeks, 3 months and 6 months to assess long term effects of AR.

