### Loss to follow-up

Participants who fail to attend clinic and do not respond to our telephone calls will be classed as smokers for the analysis of smoking abstinence, as is standard [39]. We expect to make contact with more than 90% of people at 6 month follow-up, based on experiences of a recent trial [61]. We anticipate that the effects of AR on attentional bias and withdrawal phenomena will be analysed primarily in abstinent smokers, as recommended by Shiffman et al. (2004) [60], so defaulting from routine clinic appointments by failed quitters is not considered a threat on the integrity of the trial. We therefore do not require those participants who failed to maintain abstinence and abandoned their quit to continue to attend clinics except for reasons detailed below.

This study could give valuable information on what happens to attentional bias over time, how it is affected by training, how it is affected by resuming smoking, and whether the training effect is contingent on continued abstinence. Accordingly, we will ask all participants regardless of smoking status to attend the follow-up visits. Adequate compensation should increase the likelihood of attendance.

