• Proportional hazards modelling will be used to analyse the median time to lapse by trial arm; hazard ratios (HRs) will be reported with corresponding 95% CIs. These analyses will be performed using Stata 12.0 (StataCorp, 2011, College Station, TX: StataCorp LP).

• Additional analyses

• We will adjust analyses of attentional bias scores, MPSS-C scores and MPSS-M scores for potential moderators of attentional bias, urge to smoke and withdrawal symptoms. These will include age, gender and FTND across all analyses. Pre-quit urge to smoke will also be examined in the model of attentional bias scores and pre-quit attentional bias in the models of MPSS-C and MPSS-M.

• To investigate longer-term retraining effects, we will analyse 8 week, 3 month and 6 month post-quit data for attentional bias scores using ANCOVA and mixed-effects regression models for MPSS-C scores and MPSS-M scores, as stated previously.

• To examine AR effects on cue-induced craving, VAS scores will be analysed in the same way as MPSS-C and MPSS-M scores, in mixed-effects regression models. Visual analogue scale scores will be calculated from measurements taken from a 0–100 mm scale before and after the cue exposure task, which are administered 1 week before quit day and again at 4 weeks, 8 weeks and 3 months post-quit. The difference between pre and post measurements will be calculated and the change in cue-induced craving over time will be reported.

• Generalisation of AR to other cognitive bias measures will be assessed using RT scores from the pictorial Stroop task. Stroop bias scores will be calculated by subtracting median RTs to probes that replace neutral pictures from median RTs to probes that replace smoking-related pictures. Slower RTs towards smoking-related pictures indicate a bias towards smoking cues. Again, parameters for outlying RTs do not need to be defined as median rather than mean RTs will be used. Bias scores, as measured at 4 weeks post-quit, will be used to examine AR effects on Stroop bias firstly by trial arm and secondly by abstinence status using ANCOVA.

• Similarly, we will assess whether AR generalises to untrained novel stimuli that only appear in the assessment versions of the visual probe task and not during training sessions. Attentional bias scores for the trained and untrained stimuli will therefore be analysed separately using ANCOVAs.

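### The 1-hour no-smoking condition before cue exposure is set for week −1 only, so relapsed participants' later craving ratings are not taken under the baseline condition (minor).

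*Protocol article*

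**What the plan says.** In the Protocol article, Clinic Tasks (cue exposure task), the procedure is scheduled five times: "At 1 week prior to quit day, 4 weeks post-quit and follow-up sessions at 8 weeks, 3 months and 6 months, participants in both groups". The pre-visit condition is attached to the first of these only: "Prior to attending the session at week −1, participants will be instructed to abstain from smoking for at least 1 hour". The reason follows directly: "We chose an abstinence period of 1 hour to avoid floor effects in craving ratings, commonly found immediately after smoking".

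Other trial outcomes defines change in cue-induced craving "at 4 weeks, 8 weeks, 3 months and 6 months post-quit day in abstinent and non-abstinent smokers across both trial arms". Loss to follow-up adds that "we will ask all participants regardless of smoking status to attend the follow-up visits". Analysis fits mixed-effects models to the visual analogue scale (VAS) scores and states: "The difference between pre and post measurements will be calculated and the change in cue-induced craving over time will be reported".

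For the adjusted analyses of attentional bias, urge and withdrawal, Analysis names these covariates: "These will include age, gender and FTND across all analyses". Time since last cigarette is not among them. Exhaled carbon monoxide (CO) is taken at each session and lapses are recorded, but the article describes no record of how long before a visit a participant last smoked.

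**The concern.** The article gives a condition and a reason for it, then applies it to one visit, although the reason covers others. At week −1 everyone is still a smoker and has been asked not to smoke for an hour. At later visits some participants will have resumed smoking, and nothing stated stops them from smoking on the way in. Their later ratings would then differ from week −1 partly because of the circumstances of measurement.

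Two readings are at stake. One is change from week −1 within participants, which is how the outcome is to be reported. The other is the comparison of abstinent with non-abstinent participants, since only the latter can arrive having recently smoked in any number. Both bear on the second study question, which asks about cue-induced craving. Time since last cigarette, if not noted at the visit, cannot be recovered reliably afterwards.

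**Working it through.** The protocol gives no sample size, standard deviation or power for cue-induced craving, so it has no figure of its own to reproduce on this outcome. The check therefore compares measurement conditions and then asks how many people could be affected.

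**1. Guaranteed time since last cigarette**

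- Week −1: at least 60 minutes before attending (Clinic Tasks).
- Later visits: no instruction. The cue task follows the visual probe task ("The task takes approximately 16 minutes") and the Stroop task (about 12 minutes). The guaranteed interval is 16 + 12 = 28 minutes, plus the short time taken by the CO reading and mood scale at the start.
- 28 / 60 = 0.47, so just under half of what was required at week −1.

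Clinic Tasks places the cue task after both bias tasks at week −1 too. Measures puts the VAS at the beginning of that session, and Table 1 lists no bias assessment there. If the VAS comes first, the guaranteed gap is 60 − 28 = 32 minutes. If the tasks come first at both, it is 88 − 28 = 60 minutes. The conditions differ either way.

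**2. How many could be affected**

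Inputs, from the paragraph closing Power calculation: 200 participants (100 per arm), 50% abstinent in control, risk ratio 1.3. These inputs reproduce the stated power of about 57%:

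- AR abstinence = 0.50 × 1.3 = 0.65; pooled proportion = 0.575.
- z = [0.15 − 1.96 × √(2 × 0.575 × 0.425 / 100)] / √(0.25/100 + 0.2275/100) = (0.15 − 0.1370) / 0.0691 = 0.188.
- Power = Φ(0.188) = 57.4%.

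Non-abstinent at week 4: placebo training (PT) 1 − 0.50 = 50%; attentional retraining (AR) 1 − 0.65 = 35%.

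These are ceilings. Non-attenders count as smokers but give no VAS rating. If a fraction *a* of the non-abstinent attend, and all the abstinent do, the smoking share among those rated is q*a* / (1 − q + q*a*), where q is the non-abstinent proportion:

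| *a* (assumed) | PT | AR |
|---|---|---|
| 1 | 50% | 35% |
| 0.5 | 0.25/0.75 = 33% | 0.175/0.825 = 21% |
| 0 | 0% | 0% |

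The last row matches the planning assumption in Power calculation that only quitters keep attending. Of those who do attend, an unknown part will have smoked within the hour.

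**3. Size, by assumption only**

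The documents give no effect of recent smoking on the pre/post VAS difference. Suppose it shifts that difference by 5 to 20 mm, in either direction, in every non-abstinent participant, with all attending and the same shift in both arms:

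- PT mean: 0.50 × 5 to 0.50 × 20 = 2.5 to 10 mm.
- AR mean: 0.35 × 5 to 0.35 × 20 = 1.75 to 7 mm.
- Between arms: 0.15 × 5 to 0.15 × 20 = 0.75 to 3 mm, and 0 if relapse is equal.

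The arm means are ceilings for the assumed shifts. The between-arm range also depends on equal attendance in the two arms.

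**The case against.** The case on the other side has real force.

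- *Nobody is rated immediately after smoking.* This stands in part. The preceding tasks soften the floor effect, but they do not restore the hour that the protocol itself chose.
- *Relapsed participants may not be there.* This stands in part, mostly for week 4. The request to attend whatever one's smoking status concerns follow-up visits, which Trial procedures places at 8 weeks, 3 months and 6 months. Even so, the outcome definition includes non-abstinent smokers at 4 weeks as well.
- *Analyses are primarily in abstinent smokers.* Loss to follow-up says this of attentional bias and withdrawal phenomena. An abstinent-only analysis would largely avoid the problem, but the cue-craving outcome is expressly defined in both groups.
- *Smoking exposure is documented.* CO and lapse records exist. They show whether someone smokes, not how long before the visit.

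A reader might also infer that the randomised comparison is confounded, that craving in the placebo arm is pushed down more, and that a true benefit of retraining is masked. The documents do not support this. Smoking recency arises after randomisation and shifts the arm contrast only if relapse, attendance or recency differs by arm. The analysed quantity is a within-session difference: recent smoking may lower both ratings, and a lower starting rating leaves more room to rise. The direction is therefore unknown. Nor may 50% against 35% be read as the share who have just smoked.

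**Conclusion.** The point holds as a gap in standardisation. Week −1 is measured under a stated smoking condition. The later ratings of relapsed attenders are not, with about 28 minutes guaranteed in place of 60. Comparability is weakened for change from week −1 and for the comparison by abstinence status. The AR against PT contrast is affected only under the differences by arm named above.

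The documents support neither a direction nor a size. The millimetre ranges rest wholly on an assumed 5 to 20 mm shift, and the shares on the protocol's week-4 abstinence assumptions; no rate is given for the later visits. The severity is minor: cue-induced craving is listed under other outcomes in a trial described as exploratory, and no primary or secondary outcome depends on it.

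**What to change.** In Clinic Tasks, state the 1-hour pre-session condition for every cue-exposure visit (week −1, 4 weeks, 8 weeks, 3 months, 6 months) for any participant who is smoking. Word it so that it does not imply permission to smoke, and deliver it through the telephone and text reminders already planned. Add time since last cigarette to the case report form at each of these visits. Use it descriptively, or in a sensitivity analysis of change from week −1 and of the comparison by abstinence status.

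The cost is a sentence in the protocol, a line in the reminder and one form field. Compliance will be imperfect, and staff may not know beforehand who has relapsed, so the wording must suit everyone who receives it. If only one part can be adopted, recording time since last cigarette is the simpler.

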### Control group

Participants allocated to the control group will carry out 5 weekly sessions of PT, starting 1 week prior to their designated quit day. During each session, participants perform 8 practice trials of neutral picture pairs followed by 192 trials of PT, presented in a block of two. Between each block, participants are permitted to have a short break if required. The task takes approximately 16 minutes to complete. On each PT trial, the visual probes always replace smoking-related and neutral pictures with equal frequency.

### Intervention group

Participants allocated to the AR group will carry out 5 weekly sessions of the modified visual probe task, AR, starting 1 week prior to their designated quit day. Eight practice trials of neutral picture pairs are presented prior to the first block of AR trials. A total of 192 training trials are presented in a block of two, where participants have the opportunity to have a break in between. The task takes approximately 16 minutes to complete.

The AR program differs from the PT program only in the location of the visual probes. During each training trial, visual probes always appear in the location of the neutral pictures. Thus, participants always have their attention directed away from smoking-related pictures.

### Stop smoking treatment

Systematic reviews have shown that some behavioural and pharmacological interventions increase people’s chances of successfully stopping smoking [53,54]. All participants will therefore be given NRT and receive standard withdrawal orientated behavioural support [38].

Participants in this trial will be offered 21 mg/24 hour nicotine patches as the only choice of treatment. This is because:

1) All participants will be regular smokers for whom the 21 mg dose is deemed appropriate.

2) The study aims to examine the effects of AR on urge to smoke. Short-acting NRT e.g. inhalator or gum affect cue-induced urges to smoke and reduce their intensity [55]. It would thus be difficult to assess the effects of the AR if short-acting NRT is used. Participants are also not permitted to use varenicline for the same reason [56]. Investigators have found that nicotine patches do not protect against cued craving [57], therefore we consider that patch-use is unlikely to mask the potential effects of retraining.

3) The patch is the best tolerated form of NRT and has the highest adherence [58,59].

### Dose alteration procedure

Nicotine patches are well tolerated in the large majority of regular smokers and so we expect that most people will continue with the standard dose. However, there are circumstances when the form or dose of the preparation needs to be changed. This variation reflects pragmatic behaviour in the NHS SSS and is expected to be equal in both arms. We anticipate the following occurrences:

1) Minor skin irritation to the patch is one of the most common problems with use. This is commonly eased by swapping from one form of patch to another, because it is usually intolerance to the glue. If the skin reaction is worse, such as causing blisters that cannot be remedied by emollients and hydrocortisone cream, patch use will be stopped and the participant will be swapped to an equivalent dose of oral NRT.

2) Sleep disturbance or vivid dreaming is also one of the most common problems with use of the nicotine patch. This can usually be eased by removing the nicotine patch an hour or so before bedtime and so this will be advised. There is no good evidence that 16 hour patch use is less effective than 24 hour patch use.

3) Possible symptoms that dose is too high are uncommon problems, but possible. Nausea is the earliest symptom of overdose, but it is also a common symptom experienced by people often enough. Nicotine has a short half life, meaning that by about 10 hours after first applying a patch, nicotine has reached a steady state. Therefore nausea occurring for the first time days after starting treatment is unlikely to be due to the patch. More definite symptoms are as follows, muscular twitching, dizziness, confusion, rapid pounding heart, high blood pressure, vomiting, and weakness. However, 21 mg/24 hour patch systems come as 14 mg/24 hours and 7 mg/24 hours, which can be used in a step down system. If the therapist thinks that an overdose is likely, the precaution will be to step down the dose to the next step i.e. from 21 mg to 14 mg, or from 14 mg to 7 mg.

### Duration of treatment and instructions for use

Treatment with NRT will start either on the evening prior to quit day or the morning of quit day, depending on personal preference. Patches will be dispensed accordingly during the second visit, which is 1 week prior to quit day. Instructions for patch use include changing it every 24 hours, using a different area of skin for the new patch. Participants will be advised to continue using the patch for at least 8 weeks or stop if they abandon their quit attempt before the 8 weeks. The therapist in consultation with the patient may choose to step down the patch as discussed above. Step down is not necessary as there is no evidence to suggest that it enhances efficacy, but it is commonly perceived as helpful by patients. Step down towards the end of treatment will not be permitted to commence until at least 4 weeks after quit day. The therapist will be instructed not to suggest stepping down in people who have had recent lapses. Some organisations we are working with do not allow treatment for longer than 8 weeks, but, in those that do, the therapist should consult the participant about longer courses of treatment up to 12 weeks duration. This decision will be at the discretion of the therapist in consultation with the patient.

Behavioural support will start 2 weeks prior to quit day, and last up to 4 weeks after quit day. This follows the typical 7-session withdrawal orientated therapy programme offered in existing NHS SSS [38].

### Reporting of adverse events

This is not a trial of an investigational medical product. We are using a licensed medical product within the terms of its license and in accord with clinical guidelines. We therefore expect relatively few problems and so there are no special reporting requirements. The therapist leading the sessions will manage problems within his/her own competence. Clinical advice will be sought from the trial doctor. Between them, the therapist and trial doctor will decide how to manage unexpected problems and whether to report a suspected unexpected serious adverse reaction (SUSAR) to the Medicines and Health Care Regulatory Authority using the yellow card system (this is a standard system for reporting unusual reactions to medication).

However, for the purposes of the trial, we will record clinically significant adverse events that lead to a change in medication management or is considered to be significant otherwise. This will allow us to track changes in medication instruction, such as swapping to 16 hour use or dose alterations. The CRF will be used to record the date, the nature of the adverse event/symptoms, and the action taken.

